#### Exclusion criteria

(i) Age less than 18 years

(ii) Unable to give informed consent.

(iii) Unable to speak English. Fluency in English is necessary to complete the assessment instruments (many of which have not been validated in non-English languages) and to fully participate in the development of the Joint Crisis Plans.

(iv) Primary diagnosis of psychosis

(v) Current in-patients will not be recruited to avoid any perceived potential coercion to participate, nor any patient subject to a compulsory community treatment order.

No other exclusions will be made, to maximise the external validity of the trial.

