### Eligibility criteria

#### Inclusion criteria

i) Age greater than or equal to 18 years

ii) Current contact with a Community Mental Health Team (CMHT)

iii) A primary diagnosis of DSM-IV Borderline Personality Disorder

iv) An episode of self-harm in the previous year

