### Recruitment and baseline procedures

The research team will approach local Community Mental Health Teams (CMHTs) and present the study to staff, allowing them to ask questions and become familiar with the study. Team managers will then be asked to identify all potentially eligible participants under the care of their team. Research workers will then approach potential participants through their care coordinator and invite them to a meeting in order to discuss the study in detail. At this meeting they will be given a full description of the study and provided with a written information sheet. If willing to participate, they will be invited to sign the consent form. A baseline interview will then be conducted by the research worker, either at this point or at a subsequent meeting depending on the wishes of the participant. In a pilot study of 13 participants (described further below) in which feasibility of administering the intervention and collecting data were examined, the average duration of the baseline interview was 45 minutes, with no drop-outs. Once the baseline interview has been conducted, the participant will be randomised independently, to either the intervention or control group. Figure 1 displays the flow of participants through the trial.

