### Intervention

#### Development of the experimental intervention

The JCP was originally developed for patients with psychotic illnesses. For the purposes of this study, the JCP template and procedure needed to be altered in order to make it relevant to people with BPD. For example, the original JCP template used constructs such as "relapse" which are less applicable to people with BPD. Adaptation of the JCP was informed by three distinct phases. Firstly, a series of focus groups was convened with mental health professionals and service users during which necessary adaptations were discussed. After the JCP template was amended on the basis of the feedback from the focus groups, the amended version was emailed out to members of the focus groups for further refining. Secondly, an email consultation exercise was conducted with leading UK clinical academics (n = 16) to assess the relevance of each item in the JCP menu. The final JCP template contained information for the service user, information for health professionals and details of practical help which the service user might require when in a future crisis. The procedure for developing a JCP for patients with a psychotic illness involved a joint planning meeting with the clinical team, including a doctor, because of the likelihood of treatment preferences or refusals involving medication. However, this was considered to be less relevant to patients with BPD, so the planning meeting would take place with the care coordinator, but a doctor would be consulted if required. Finally, we examined the feasibility of conducting JCP planning meetings and data collection methods with a small convenience sample of BPD service users (n = 13). Results from this case series indicated that not only was the process of developing JCPs feasible, but also that the JCPs were potentially useful - participants in the case series reported using the JCPs when experiencing crises, with some stating that they had reduced their self-harming behaviour since creating their JCP.

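### The closed exclusion list lets someone who already holds a Joint Crisis Plan from the development case series be randomised to treatment as usual

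*Protocol article*

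**What the plan says.** The Inclusion criteria section sets an age limit and three further conditions: "Current contact with a Community Mental Health Team (CMHT"), "A primary diagnosis of DSM-IV Borderline Personality Disorder" and "An episode of self-harm in the previous year". The Exclusion criteria section lists five items: age under 18, inability to consent, inability to speak English, primary psychosis, and current in-patient status or a compulsory community treatment order. It then closes the list: "No other exclusions will be made, to maximise the external validity of the trial".

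The section Development of the experimental intervention reports that the team tested planning meetings and "data collection methods with a small convenience sample of BPD service users (n = 13"). It adds that "participants in the case series reported using the JCPs when experiencing crises, with some stating that they had reduced their self-harming behaviour" after making their plan.

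The Overview calls the trial single-centre. Under Recruitment and baseline procedures the team approaches local community mental health teams, and "Team managers will then be asked to identify all potentially eligible participants under the care of their team". That section describes no check for an existing plan. The Control intervention section defines TAU as routine care with a prescriptive crisis contingency plan, which is a different document from a JCP.

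**The concern.** The article itself identifies people who have been through the experimental procedure, and they belong to the target population. Because the exclusion list is declared complete, the rule as written admits them.

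A prior holder allocated to TAU is not receiving the comparator that the Control intervention section describes. That person's self-harm risk may already reflect the plan, which lowers the TAU event rate and shrinks the difference. A prior holder allocated to the JCP arm would repeat the procedure, which does little to the contrast. The net bias is therefore toward no difference. The trial is meant to estimate a range of effects and inform a definitive trial, so a diluted estimate would be carried forward.

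The stated reason for closing the list, external validity, does not call for admitting these people. The Abstract says JCPs had not been used in this disorder to date, so prior holders do not represent a routine patient group.

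**Working it through.** **Inputs.** From Power calculation: TAU risk 36%, JCP risk 12%, two-sided 5%, 80% power, 114 in total at 1:1, raised to 120. From Development of the experimental intervention: 13 people in the case series.

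**1. Reproduce the plan's figure.** Uncorrected n per arm, with mean risk 0.24:

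[1.960·√(2·0.24·0.76) + 0.842·√(0.36·0.64 + 0.12·0.88)]² / 0.24² = 48.5

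With the continuity correction:

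(48.51/4)·[1 + √(1 + 4/(48.51·0.24))]² = 56.5, so 57 per arm and 114 in total. This matches the article. Without the correction the total is 98, so the corrected formula is the one to use below.

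**2. Dilute the TAU risk.** If k of the 60 people in TAU are prior holders with risk r:

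TAU risk = 0.36 − (k/60)·(0.36 − r)

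The documents give neither k nor r. Two assumptions for r are shown: 12% (the full benefit in the plan) and 24% (half of it). The JCP arm stays at 12%.

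**3. Recompute power.**

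Power = Φ{[(p₁ − p₂) − 1/n − 1.960·√(2p̄(1 − p̄)/n)] / √[(p₁(1 − p₁) + p₂(1 − p₂))/n]}

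- No prior holders, n = 60: (0.2233 − 0.1528)/0.0748 = 0.942, power 82.7%.
- k = 6.5, r = 12%, n = 60: (0.1973 − 0.1499)/0.0739 = 0.642, power 73.9%.

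| Prior holders in TAU (k) | r | TAU risk | Difference (points) | Power, 60 per arm | Power, 57 per arm |
|---|---|---|---|---|---|
| 0 | – | 36.0% | 24.0 | 82.7% | 80.4% |
| 1 | 12% | 35.6% | 23.6 | 81.5% | 79.1% |
| 2 | 12% | 35.2% | 23.2 | 80.2% | 77.8% |
| 3 | 12% | 34.8% | 22.8 | 78.9% | 76.4% |
| 6.5 (all 13, even split) | 12% | 33.4% | 21.4 | 73.9% | 71.3% |
| 6.5 (all 13, even split) | 24% | 34.7% | 22.7 | 78.6% | 76.1% |

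The last column keeps the share k/60 and supposes that 57 per arm are analysed, meaning the margin from 114 to 120 is used up by missing records, as the article intends.

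**4. Bound on k.** All 13 would be 13/120 = 10.8% of the sample. With 1:1 allocation about half would fall in TAU. A chance imbalance could put more there, but the even split already supposes that every member of the series is eligible, consents and is randomised.

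**The case against.** The strongest reply is that the exposure is possible but not shown. The article calls the 13 a convenience sample and does not say where they came from. It does not say whether they are still under a community team, or whether any will be approached. That all 13 completed a plan is implied, not stated. This stands, and it makes 13 a ceiling rather than an estimate.

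The second reply also stands. Entry requires self-harm in the past year, so a prior holder who had stopped for longer than that is ineligible, and one who enters may have self-harmed despite having a plan. Giving such people the full assumed benefit is close to the most damaging case, which is why the half-benefit row is shown.

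A third reply is that the closing sentence is aimed at restrictions on patient type, and that screening out a short pilot list is an operational matter for the full protocol. This is weaker. The article does not leave the matter open; it says that there are no other exclusions. The trial's exploratory status limits the consequence but does not make the rule right.

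Three stronger readings are tempting, and the documents do not support them:

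- A reader might infer that baselines measured after an earlier plan spoil a change-from-baseline analysis. The Statistical analysis plan section compares groups on self-harm during follow-up and on other outcomes at six months; it specifies no change score.
- A reader might infer that pilot participants are especially likely to enrol. Nothing in the article says so.
- A reader might infer that service users in the focus groups were also treated. They discussed and refined a template, and nothing shows that they received a JCP.

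**Conclusion.** The concern holds as a defect in the written rule: the eligibility criteria allow a person who already has the experimental plan to be randomised to TAU. The documents do not show that this will happen, or to how many people.

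The likely effect is small. With one or two prior holders in TAU, power at 60 per arm is about 80–82% instead of 83%. The loss to about 74% requires all 13 to enter, an even split and the full 24-point benefit. At half that benefit, power is about 79%. These figures rest on the plan's own event rates and on assumed values for the number and risk of prior holders. They should be read as a range up to a ceiling, not as an expected loss. This is a cheap improvement and does not threaten the trial.

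**What to change.** Add a sixth item to the Exclusion criteria for anyone who already has a Joint Crisis Plan or took part in the JCP case series, and reword the closing sentence to say that no further exclusions will be made. Before randomisation, check each candidate against the pilot list and the electronic record.

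State that two groups remain eligible: focus-group members who have no JCP, and people with the routine crisis contingency plan, which is part of TAU.

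The cost is one line of eligibility text, one screening check and the loss of at most 13 candidates. Sample size and analysis are unchanged.

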### Recruitment and baseline procedures

The research team will approach local Community Mental Health Teams (CMHTs) and present the study to staff, allowing them to ask questions and become familiar with the study. Team managers will then be asked to identify all potentially eligible participants under the care of their team. Research workers will then approach potential participants through their care coordinator and invite them to a meeting in order to discuss the study in detail. At this meeting they will be given a full description of the study and provided with a written information sheet. If willing to participate, they will be invited to sign the consent form. A baseline interview will then be conducted by the research worker, either at this point or at a subsequent meeting depending on the wishes of the participant. In a pilot study of 13 participants (described further below) in which feasibility of administering the intervention and collecting data were examined, the average duration of the baseline interview was 45 minutes, with no drop-outs. Once the baseline interview has been conducted, the participant will be randomised independently, to either the intervention or control group. Figure 1 displays the flow of participants through the trial.

**Figure 1 F1:**
[figure not shown]
**CONSORT flow chart of JOSHUA trail design**.

### Randomisation procedure and methods to minimise bias

Participants will be randomised using the method of minimisation with a random component stratified by alcohol misuse [as measured by the Alcohol Use Disorders Identification Test (AUDIT) [13]] and depression [as measured by the Hospital Anxiety and Depression Scale (HADS) [14]]. The randomisation will be managed by the Clinical Trials Unit (CTU) at the Institute of Psychiatry. Confirmation of eligibility, consent, and baseline data will be obtained prior to randomisation. Bias in the recruitment and randomisation process will be avoided by having randomisation done centrally by the CTU, and hence concealment maintained from the investigators, and by keeping a log of all service users randomised and including them all in the analysis. The research worker collecting outcome data will be blinded to the allocation. Some outcome data will be obtained from electronic patient records, even for participants lost to follow-up interview. This will include any episodes of self harm, hospital admissions and service use recorded in the electronic records. Bias in the collection of outcome data will also be minimised by the use of standardised objective assessments and by blinding the researchers as far as possible to service user allocation. There will be specific instructions to participants and clinical teams not to disclose the treatment details of any study participant. Every effort will be made to maximise the single blindness of research workers, whose 'best guesses' of treatment arm status will be assessed after the final assessment in order to test whether their blindness was successfully maintained.

### Intervention

#### Development of the experimental intervention

The JCP was originally developed for patients with psychotic illnesses. For the purposes of this study, the JCP template and procedure needed to be altered in order to make it relevant to people with BPD. For example, the original JCP template used constructs such as "relapse" which are less applicable to people with BPD. Adaptation of the JCP was informed by three distinct phases. Firstly, a series of focus groups was convened with mental health professionals and service users during which necessary adaptations were discussed. After the JCP template was amended on the basis of the feedback from the focus groups, the amended version was emailed out to members of the focus groups for further refining. Secondly, an email consultation exercise was conducted with leading UK clinical academics (n = 16) to assess the relevance of each item in the JCP menu. The final JCP template contained information for the service user, information for health professionals and details of practical help which the service user might require when in a future crisis. The procedure for developing a JCP for patients with a psychotic illness involved a joint planning meeting with the clinical team, including a doctor, because of the likelihood of treatment preferences or refusals involving medication. However, this was considered to be less relevant to patients with BPD, so the planning meeting would take place with the care coordinator, but a doctor would be consulted if required. Finally, we examined the feasibility of conducting JCP planning meetings and data collection methods with a small convenience sample of BPD service users (n = 13). Results from this case series indicated that not only was the process of developing JCPs feasible, but also that the JCPs were potentially useful - participants in the case series reported using the JCPs when experiencing crises, with some stating that they had reduced their self-harming behaviour since creating their JCP.

#### Administration of the experimental intervention

In the trial, a clinically experienced research worker will organise a meeting with each participant randomised to receive a JCP. The research worker will introduce a list of topics to be considered for inclusion in the JCP and will then organise a meeting between the participant and their care coordinator, when the JCP contents will be finalised. The research worker will then produce a typed version of the JCP and copies will be sent to all those whom the participant specifies. A copy of the JCP will also be attached to each participant's electronic psychiatric case record in order to maximise dissemination of the plan.

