### Self-harm follow-up data

Variables (i) and (ii) will be gathered from the following sources:

1. The follow-up interviews with participants at 6-months - participants will be asked to recall the approximate number of self-harm events occurring over the preceding six months. Variables (iii) and (iv) will be gathered using questions derived from Hawton et al [15].

2. Diaries: all participants will be supplied with a simple diary/calendar and will be asked to record all self-harm events on this (by simply circling the days of the month on which self-harm events occurred).

3. Electronic psychiatric case records.

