The JOSHUA study has limitations which warrant mentioning. Firstly, it is not a double-blind study design and, as such, the participants and certain members of the research team will be aware of which arm of the trial each participant has been allocated to. However, collection and analysis of follow-up data will be blind to treatment status. In addition there will be specific instructions to participants and clinical teams not to disclose treatment details details at any stage throughout the study. Every effort will be made to maximise the single blindness of research workers, whose 'best guesses' of service user status will be assessed after the final assessment/at the end of the study to test whether their blindness has been maintained. Secondly, there may be selective dropout in one arm of the study; as such, we will examine whether this occurred in the data analysis. Finally it is not designed as a definitive trial but one which will give broad indications of effectiveness and aid the design of a future trial.

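### The Joint Crisis Plan is filed in the electronic record that also supplies self-harm data, so blind collection is not secured for record-derived outcomes

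*Protocol article*

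**What the plan says.** Under *Administration of the experimental intervention*, "a clinically experienced research worker will organise a meeting with each participant randomised to receive a JCP", and the finished plan is then filed, with the stated aim of spreading it as widely as possible: "A copy of the JCP will also be attached to each participant's electronic psychiatric case record". The filing can concern only the JCP arm, since controls have no JCP. The crisis contingency plan described under *Control intervention* is a different document and belongs to routine care.

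Under *Randomisation procedure and methods to minimise bias*: "The research worker collecting outcome data will be blinded to the allocation. Some outcome data will be obtained from electronic patient records". The outcomes concerned are named: "This will include any episodes of self harm, hospital admissions and service use recorded in the electronic records". *Self-harm follow-up data* lists "Electronic psychiatric case records" as the third source, after interview and diary, for time to first self-harm and number of episodes.

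The limitations paragraph of the *Discussion* says that "collection and analysis of follow-up data will be blind to treatment status". The safeguards given are instructions to participants and clinical teams not to disclose treatment, and a guess of allocation by the research workers after the final assessment.

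**The concern.** A document that exists in one arm only is placed, with the aim of being widely seen, in a source from which a primary outcome is read. Deciding whether a case note describes self-harm takes judgement: the power calculation counts serious threats, and the Discussion concedes that there is no gold standard for measuring episodes. An extractor who knows the arm may read borderline entries differently.

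The record also carries weight in the plan. It supplies data for people lost to interview, the increase from 114 to 120 allows for loss in the administrative self-harm data, and the primary analysis is repeated on each source. The comparison of sources is meant to guide outcome collection in the definitive trial. If one source was read with knowledge of the arm, a disagreement between sources could reflect that knowledge rather than the method of collection.

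**Working it through.** This is settled by setting the sections side by side; no figure in the plan is at issue.

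**Step 1. The plan's own figure.** Inputs from *Power calculation*: 36% v 12%, two-sided 5%, 80% power, 1:1. Uncorrected size per arm:

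n = [1.96·√(2·0.24·0.76) + 0.8416·√(0.36·0.64 + 0.12·0.88)]² / 0.24² = (1.184 + 0.488)² / 0.0576 ≈ 48.5, or 49.

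With continuity correction:

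n′ = (48.5/4)·[1 + √(1 + 4/(48.5·0.24))]² ≈ 56.5, or 57, which gives 114 in total.

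The stated 114 is reproduced, and nothing below changes it.

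**Step 2. Does the record reveal the arm?** The JCP is filed in the record, and only the JCP arm has one. A filed JCP therefore identifies the intervention arm. Its absence points to usual care, less surely, because a JCP-arm participant might not complete a plan. With 120 randomised 1:1, 120/2 = 60, so up to about 60 people are directly identifiable.

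**Step 3. Is that record an outcome source?** Yes: for self-harm, admissions and service use, including for people who miss the interview ("Some outcome data will be obtained from electronic patient records, even for participants lost to follow-up interview").

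**Step 4. Does a stated safeguard close the route?** The non-disclosure instructions bind participants and clinical teams; they do not mask a filed document. The allocation guess can detect unblinding but cannot prevent it. Because it comes after the final assessment, a worker who has already opened the record may be guessing from the JCP itself.

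**Step 5. Who extracts, and when?** The article does not say. *Follow-up assessments* gives the interview to a blinded research worker. Record data are described in the passive, with no extractor named. Two cases follow:

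- A separate extractor: the interview stays protected, but the extractor can still see the JCP, so the Discussion's statement is not secured for the record source.
- The interviewer extracts and opens the record first: the interview ratings and the guess are exposed as well.

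**Step 6. Scale, as an illustration only.** The documents give no rate of biased coding. Assume no true effect (36% in both arms), 60 per arm, and an extractor who misses a fraction m of JCP-arm cases in the record. Then p₂ = 0.36(1 − m), and the chance of a significant result favouring JCP is Φ{[(0.36 − p₂) − 1.96·√(2·p̄·(1 − p̄)/60)] / √[(0.36·0.64 + p₂(1 − p₂))/60]}, where p̄ is the mean of the two proportions.

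| m (assumed) | p₂ | Chance of a false result favouring JCP |
|---|---|---|
| 0 | 0.360 | 2.5% |
| 10% | 0.324 | 6.1% |
| 20% | 0.288 | 13.1% |
| 30% | 0.252 | 24.8% |

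This applies to the record-based analysis only. The values of m are not predictions.

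**The case against.** The best reply is that the text claims less than it seems to. The randomisation section promises blinding of researchers only as far as is feasible, and it plans a check on whether blinding held. The Discussion admits that some of the research team will know the allocation. The record is one of three sources, the diary is filled in by participants, and discrepancies between sources will be investigated. Who extracts records, and in what order, is operational detail that a condensed article may leave to the full protocol.

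Much of this stands. Silence on the extractor and the order of work is not itself an error. What remains is a conflict between stated passages: the Discussion drops the qualifier, and the plan itself creates this exposure.

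Three stronger readings are tempting but unsupported:

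- *Blinding must fail for all outcomes.* The documents do not say that the blinded interviewer reads the records, and they do not describe the record's layout. Disclosure through an attachment is likely for record-derived outcomes but not certain. For the interview it is only a risk.
- *One recoded participant changes the result.* With 60 per arm, 21 v 11 gives p = 0.039 and 21 v 12 gives p = 0.066 by uncorrected chi-square. But that table is chosen at the boundary. With continuity correction 21 v 11 already gives about 0.063. At the predicted rates (about 22 v 7, uncorrected p = 0.0014) significance is lost only at 22 v 13, six recodings away. None of this measures bias.
- *Record-based self-harm should become a supporting analysis.* That is a debatable preference and does not follow from the conflict.

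**Conclusion.** The concern holds for record-derived outcomes. As written, the unqualified statement of blind collection in the Discussion, and the statement that the worker collecting outcome data is blinded, are not secured for self-harm, admissions and service use read from the electronic record. Up to about 60 JCP participants are identifiable by that route. The size of any bias cannot be derived from the documents, and the table above rests wholly on assumed values. Exposure of the interview ratings and the allocation guess is conditional on one worker doing both tasks and opening the record first. The conclusion assumes that the attachment is visible to someone reading the record, which fits its stated purpose of dissemination. It does not touch the sample size or the choice of analyses.

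**What to change.** 1. Complete and lock the 6-month interview, its scoring and the allocation guess before that worker opens the electronic record.
2. Extract self-harm from dated entries against fixed written criteria, without opening the care-plan or JCP attachment area.
3. Qualify the blinding statements in *Randomisation procedure and methods to minimise bias* and in the *Discussion*: interview ratings are blinded, but record-derived outcomes may not be. This is needed even with step 2, because dated notes may mention the JCP meeting. Take it into account when the three sources are compared under *Statistical analysis plan*.

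The cost is a fixed order of work and some wording, with no extra staff, visits or participants. The downside is that record extraction must follow the interview and its blinding is claimed less strongly.
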